### Statistical analysis

All base case analyses will be performed based on the ‘intention to treat’ principle. Analysis will however, also be performed based on a ‘as treated’ analysis.

#### Primary outcome

A linear mixed model will be used for the primary outcome measure VAS pain/ tingling sensations in the arm. Covariates in the model will be time as categorical, treatment and the interaction between time and treatment. The covariance model will be unstructured. The main endpoint parameter, the difference between the two arms at 1 year, will be estimated from this model. To answer the question whether the difference in effect between surgical and conservative treatment depends on de duration of complaints, this linear mixed model will be extended with extra (interaction) terms.

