### Baseline data

The baseline questionnaires and demographics will be registered before randomisation. Also the preferences of patients and doctors will be registered using a 5-point scale varying from ‘strong preference for surgery’ to ‘strong preference for conservative treatment’.

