### Randomisation procedure

A randomisation list is prepared for every participating hospital. Randomisation will take place in variable permutation blocks, which are unknown to the research nurse. A random generator is used to generate the random sequence within the blocks. The data manager, who is not involved in the selection and allocation of patients, will prepare coded and sealed envelopes containing the treatment allocation based on the pre-generated stratified random allocation list.

The research nurse will make an appointment with the participant after the visit to the neurologist or neurosurgeon. After registering baseline information, a sealed envelope with treatment allocation will be opened in front of the patient. Patients who do not wish to be randomised will be asked to participate in a cohort study, in which both surgically and conservatively treated patients will be followed.

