#### Secondary outcome measures

1. Neck Disability Index (NDI). Although the NDI is a score to monitor complaints of cervical myelopathy, it gives a reliable impression of the disability of the patient with respect to daily activities [28,29]. The scores of the items are added up and transformed into a scale of 0 to 100. A higher score reflects a better health condition.

2. VAS pain or tingling sensations in the arm at different time points (intake, 6 weeks and 3, 6, 8, 24 months).

3. VAS pain in the neck. The pain intensity in the neck will be measured with a 100 mm horizontal VAS at different time points (intake, 6 weeks and 3, 6, 8, 12, 24 months).

4. Short Form-36 (SF-36). The SF-36 will be used as a generic quality-of-life questionnaire. The questionnaire relates to the analysis of the general functional status of patients. The scores of the different topics are added up and transformed into a scale of 0 to 100. A higher score reflects a better health condition. The different topics can be summarised in a physical and psychological main domain.

5. Illness Perceptions Questionnaire – short form (IPQ-K). The Brief Illness Perceptions Questionnaire is translated from English to Dutch and adapted for differences in culture [30]. This questionnaire represents the way a patient copes with his complaints, and it gives insight in the functioning of a patient.

6. Perceived recovery. To measure perceived recovery a seven-point Likert scale will be used [31]. The scores on this scale vary from ‘completely recovered’ to ‘worse than ever’. The scales will be completed by the patient, research nurse, and the neurologist or neurosurgeon.

7. Health state utility VAS. Patients will assess how they value their health using a VAS ranging from 0 = as bad as death to 100 = perfect health.

8. DS-14. This Dutch questionnaire determines the extent of ‘Distressed-personality’ of the patient. A type D personality is defined in medical psychology as the co-existent presence of both negative affectivity (e.g. worrying, irritability, gloom) and social inhibition (e.g. reticence and a lack of self-assurance). The questionnaire consists of seven questions concerning negative affectiveness and seven questions concerning social inhibition. Individuals that score on both dimensions 10 or higher are being classified as having a type D personality. A type D personality has been demonstrated to have a negative influence on outcome of disease [32,33].

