### Sample size

For the primary research question, the sample size is based on the standard deviation of VAS arm pain, which is estimated between 25 and 30, as reported by Persson after 1 year of follow-up [20]. If we consider an α = 0.05 and a power of 90%, and we take 15 mm difference in VAS pain in the arm as clinically relevant, then we need 100 patients in both groups (including a 10% compensation for lost to follow-up) in a worst case scenario of a standard deviation of 30 to show such a difference as statistically significant under the null hypothesis. Because the analysis for the secondary question requires more patients than the primary research question, the sample size is chosen with regard to the secondary research question. In order to investigate the modifying effect of the (pre-randomisation) duration of pain (X, in months) on the treatment effect (T) a covariance-analysis will be performed with the VAS measured after 12 months follow-up as a dependent variable and T, X and the interaction T*X as independent variables. The coefficient of T*X represents the increase (or decrease) of the treatment effect per month duration of pain on baseline. The standard error of the slope of this regression line is $\sqrt{\left(1-\rho^{2}\right)}\sigma_{\mathrm{vas}}/\left(\sqrt{n-1}\sigma_{x}\right)$, in which ρ is the correlation between the duration of pain at baseline and the VAS after 12 months follow-up, σ_VAS_ the SD of the VAS after 12 months follow-up and σ_X_ the SD of the duration of pain at baseline. Based on the RCT by Persson [20] the σ_VAS_ is estimated conservatively at 30 mm and the SD of the duration of pain at baseline conservatively at 25. We are not informed about the correlation, but ρ = 0 leads to a conservative estimate of the standard error of the slope. Because this correlation is probably small, the overestimation of the sample size is probably limited (for instance 1% if ρ = 0.1 or 4% if ρ = 0.20). The number of patients needed for a power 1-β = 0.80 and two-sided significance level of α = 0.05 can be calculated as $n_{\mathrm{pergroup}}-1={\left(1.96+0.84\right)}^{2}\cdot 2\sigma^{2}/\Delta^{2}$, in which σ = σ_VAS_/σ_X_ and Δ is the increase of the difference in slope per month. An increase in the difference in slope of 4 mm per year duration of pain at baseline is considered as clinically relevant. According to the formula above, 200 patients per study arm are needed, adding up to a total of 400 patients.

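### The primary mixed model is valid but uses neither the intake VAS nor hospital, and so gives up precision that would cost nothing to gain

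*Protocol article*

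**What the plan says.** The section Statistical analysis, Primary outcome, gives the model terms: "Covariates in the model will be time as categorical, treatment and the interaction between time and treatment". It adds "The covariance model will be unstructured", and of the estimand it says "The main endpoint parameter, the difference between the two arms at 1 year, will be estimated from this model". For the duration question this model is to be extended with further interaction terms. The Sample size section plans that question as a regression of 12-month VAS on treatment, duration and their product.

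Both unused variables are available. Under Baseline data: "The baseline questionnaires and demographics will be registered before randomisation". Secondary outcome measures lists "VAS pain or tingling sensations in the arm at different time points (intake, 6 weeks and 3, 6, 8, 24 months", and the follow-up table also shows the VAS at intake. Under Randomisation procedure: "A randomisation list is prepared for every participating hospital", with envelopes prepared from a "pre-generated stratified random allocation list". Hospital is the only stratum described.

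No other section adds intake arm VAS or hospital to the primary model. The prognostic variables under Secondary outcome enter only to study effect modification, and neither of these two is among them.

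**The concern.** A baseline measurement of the outcome usually predicts the follow-up value, and a stratification factor may do so too. Leaving both out keeps variation in the residual that could have been explained.

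It is easy to assume that a repeated-measures model with unstructured covariance adjusts for baseline once intake is one of its visits. With a free treatment term and a free treatment-by-time term it does not, because each arm keeps its own intake mean.

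Two results are affected. The Conclusion and Discussion hypothesises that the two strategies give comparable results at one year, and how firmly the trial can support that depends on the width of the confidence interval. The duration interaction determines the sample size and was planned at 80% power, so it has little to spare.

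**Working it through.** **Inputs from the protocol (Sample size).** SD of 12-month VAS 30 mm; difference 15 mm; α 0.05, two-sided (stated for the second question, assumed for the first); 200 per arm; SD of duration 25 months; interaction 4 mm per year; 10% loss to follow-up, stated for the first question only.

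**Inputs assumed.** Correlation r between intake and 12-month VAS of 0.2 to 0.5. Share of variance due to hospital (ICC) of 0.02 to 0.10. The document gives neither.

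**1. The plan's own power.** SE = 30 × √(2/200) = 3.00 mm. Power = Φ(15/3.00 − 1.96) = Φ(3.04) = 99.88%. The stated figure of above 99% reproduces.

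**2. Does including intake as a visit adjust for it?** A simulation used 200 per arm, r = 0.4 and 200 runs. It compared free arm-by-time terms with a model that gives both arms a common intake mean.

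| Data | Model | SE (mm) | Correlation of estimate with chance intake difference |
|---|---|---|---|
| Complete | Free arm-by-time | 3.00 | 0.38 |
| Complete | Common intake mean | 2.75 | 0.01 |
| 10% dropout | Free arm-by-time | 3.10 | 0.46 |
| 10% dropout | Common intake mean | 2.85 | 0.08 |

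With complete data, the free model's 1-year contrast matched the raw 12-month difference to about 1e-11. With dropout it no longer equals the raw difference, but its SE is still the larger of the two.

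**3. Gain for the primary contrast.** Adjusted SE = 3.00 × √(1 − r²). Half-width = 1.96 × SE, which is 5.88 mm unadjusted. Equivalent unadjusted n per arm = 200/(1 − r²).

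| r | Variance reduction | SE (mm) | Half-width (mm) | Equivalent n per arm |
|---|---|---|---|---|
| 0.2 | 4% | 2.94 | 5.76 | 208 |
| 0.3 | 9% | 2.86 | 5.61 | 220 |
| 0.4 | 16% | 2.75 | 5.39 | 238 |
| 0.5 | 25% | 2.60 | 5.09 | 267 |

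Power for 15 mm moves only from 99.88% to 99.92% at r = 0.2 and 99.99% at r = 0.5.

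A chance intake difference of 1.96 standard errors shifts the unadjusted estimate by 1.96 × r × 3.00 mm. That is 1.2 mm at r = 0.2, 1.8 mm at 0.3 and 2.9 mm at 0.5, whatever the intake SD.

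**4. Duration interaction.** The protocol's formula gives n − 1 = (1.96 + 0.84)² × 2 × (30/25)² / (4/12)² = 203.2, so n ≈ 204 against the stated 200. The SE of the interaction is (30/25) × √(2/(n − 1)), and power is Φ((4/12)/SE − 1.96). Adjustment multiplies the SE by √(1 − r²), taking r as the correlation that remains after treatment and duration.

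| n per arm | Unadjusted | r = 0.2 | r = 0.3 | r = 0.5 |
|---|---|---|---|---|
| 200 | 79% | 81% | 83% | 89% |
| 180 (10% loss assumed) | 75% | 76% | 79% | 86% |

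**5. Hospital.** When stratified allocation is ignored, the SE is overstated by a factor of about 1/√(1 − ICC): 1.010, 1.026 and 1.054 for ICC 0.02, 0.05 and 0.10.

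**The case against.** The strongest reply is that nothing here is wrong. In a randomised trial the stated model estimates the 1-year difference without bias, and its SE is valid. This stands. A reader might infer that chance baseline imbalance biases the result. It does not: such imbalance is sampling variation and is already inside the confidence interval. Nor does ignoring the strata inflate type I error, since the SE errs on the wide side.

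A reader might also infer that the primary comparison lacks power. The document does not support that, because power for 15 mm is above 99% with or without adjustment.

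The size of the gain rests on an undocumented correlation. The entry criterion of at least 40 mm on arm pain or tingling narrows the intake range and may lower it; at r = 0.2 the variance gain is only 4%. This stands, and is why the low end is shown. Likewise, 75% power for the interaction applies a 10% loss that the protocol states only for the first question. Without that loss the figure is 79%, close to plan.

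It is also too strong to say that the model gains nothing from intake data. The equality with the raw difference holds for complete data. With dropout, earlier visits contribute through the covariance, although the arms' intake means remain free.

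Last, an article condenses, and a separate analysis plan might add covariates. But the article does state the model's terms. The point is an improvement to a method it specifies, not a complaint that detail is missing.

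**Conclusion.** The point holds as one of efficiency, not validity. The stated model is unbiased with a slightly conservative SE, and it forgoes precision from two variables already in hand.

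For an assumed r of 0.2 to 0.5, the loss is 4% to 25% of residual variance, or 0.12 to 0.79 mm of confidence interval half-width at 200 per arm with complete data. This is small against 15 mm and does not change the power of the primary test. It matters more for the claim of comparable results and for the duration interaction, where power at 200 per arm would rise from about 79% to between 81% and 89%. The hospital component is probably small, at about 1% to 5% of the SE for an assumed ICC of 0.02 to 0.10; the article gives neither the ICC nor the number of hospitals.

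**What to change.** Amend the Primary outcome analysis in one of two equivalent ways:

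- model the post-randomisation visits with baseline VAS and baseline VAS × time as covariates; or
- keep intake as a response and constrain the two arms to a common intake mean.

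In either case add hospital as a fixed effect, or as a random effect if there are many small centres. Carry the same terms into the duration-interaction model. In the secondary-outcome models, use each outcome's own baseline value where one is collected, not the arm VAS.

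The cost is one or two sentences, with no new data, visits or patients. If the change is fixed before outcome data are examined, it also removes later discretion over which adjustment to report.

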#### Secondary outcome

Secondary outcomes will be analysed for differences between groups with linear mixed models similar to the main endpoint. Furthermore, we will investigate whether potential prognostic variables (gender, age, presence of neck pain, more neck pain than arm pain, Valsalva manoeuvre test, Spurling test, shoulder abduction test, type of personality based on DS-14 and based on IPQ-K, anterior or posterior approach, smoking, neurological deficits (strength on an 1–5 Medical Research Council (MRC) scale and sensibility), duration of the symptoms, Quetelet index) are associated with the difference between the treatment arms in the primary endpoint. This will be carried out by adding a potential prognostic variable and its interaction with the treatment arm to the linear mixed model.

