### Interventions

#### Group A: Surgical intervention

Surgery will take place within 2–4 weeks of randomisation. ‘Usual care’ will be pursued. Therefore the surgeon can perform the surgery he prefers, with the exception of implantation of an artificial disc. Variables of the procedure are filled in a standardised form.

For anterior discectomy, the level of surgery is verified by fluoroscopy. The operation will be carried out by a qualified neurosurgeon. Most surgeons operate using loupe magnification. The platysma muscle is separated or cleaved at the right side of the midline (less frequently on the left side), and the prevertebral space is reached by an approach medial to the sternocleidomastoid muscle and the carotid artery, and lateral to the trachea and oesophagus. The disc is incided and the corpora are distracted. Discectomy is performed as thorough as possible. Regularly the posterior ligament is cut and the spinal root is decompressed. If necessary, spondylarthrotic rims are removed. To the preference of the surgeon bone graft or an intervertebral fusion device is left behind. Decompression of more levels is allowed. If the surgeon prefers to decompress the cervical nerve root from the dorsal side it is allowed to perform a dorsal foraminotomy. The muscles of the neck are unilaterally detached at the site of interest. With a high-speed drill a foraminotomy is performed to decompress the nerve.

The postoperative care will be performed according to ‘usual care’ and will regularly be a stay in the hospital for one or two days, without physiotherapeutic treatment. If possible most patients will gradually return to work within weeks after the surgical intervention.

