#### Group B: Conservative management

Management of the conservative arm will be performed according to usual care by either the neurologist or general practitioner (GP). In the Netherlands, formal guidelines for this approach are lacking, however, related guidelines for lumbar radicular syndrome exist. The treatment of CRS is aimed primarily at pain relief and maintenance/restoration of normal day-to-day activities. Various studies have shown that adequate and unambiguous information about the problem from which the patient is suffering (the nature of the condition) and what the patient can expect (the prognosis), together with trustworthy counselling can reduce the anxiety and uncertainty felt by the patients Usually, no soft collar nor physiotherapy is prescribed, however it is allowed. A graded activity time schedule is made beforehand together with the patient [24,25].

In case of progressive neurological deficit or worsening intolerable pain the GP or neurologist can refer the patient back to the research nurse or neurosurgeon in order to consider surgery. If, six months after randomisation, the patient has still not improved or suffers from disabling intermittent CRS, surgical treatment will be offered.

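### Surgical approach is tested as a modifier of the between-arm difference, but it exists only in operated patients, so its interaction with arm is either not identified or does not describe the intention-to-treat effect

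*Protocol article*

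**What the plan says.** In the protocol article, under Statistical analysis, Secondary outcome, a list of potential prognostic variables is to be examined for whether they "are associated with the difference between the treatment arms in the primary endpoint". The list includes "type of personality based on DS-14 and based on IPQ-K, anterior or posterior approach, smoking". One method is given for every item: "adding a potential prognostic variable and its interaction with the treatment arm to the linear mixed model". Approach gets no separate handling.

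Other sections show where approach comes from:

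- **Group A: Surgical intervention.** It is the operator's decision ("Therefore the surgeon can perform the surgery he prefers, with the exception of implantation of an artificial disc"), with a dorsal foraminotomy allowed as the alternative to anterior discectomy. It is documented with the operation: "Variables of the procedure are filled in a standardised form".
- **Group B: Conservative management.** Surgery is not the allocated treatment. It can be considered earlier for progressive deficit or worsening, intolerable pain, and later: "If, six months after randomisation, the patient has still not improved or suffers from disabling intermittent CRS, surgical treatment will be offered".
- **Baseline data.** Patients' and doctors' preferences are recorded on a five-point scale running from surgery to conservative care. No intended approach is mentioned.
- **Statistical analysis.** Intention to treat is the base case, with an additional as-treated analysis.
- **Conclusion and Discussion.** Some group A patients are expected to recover before their operation, and some group B patients to be operated before six months.

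**The concern.** An interaction between a variable and randomised arm answers the question of whether the effect of allocation differs between levels of that variable. The variable must therefore have a value in both arms, and that value should not depend on what happened after allocation. The other listed items are patient characteristics that can be known at entry in everyone. Approach is a property of an operation. It is settled after allocation, by the surgeon, and has no value in a patient who is never operated.

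Identifying factors that favour one treatment is a stated aim of the trial. A coefficient for approach printed beside those for age, smoking or neck pain would look like the same kind of evidence. It would rest on groups formed after randomisation, and could mislead mainly about operative technique.

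**Working it through.** **The plan's own figures.** No figure is given for the approach interaction. The only interaction that is sized is treatment by symptom duration (Sample size): SD of the VAS 30 mm, SD of duration 25, relevant change 4 mm per year = 4/12 mm per month, two-sided α 0.05, power 0.80.

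n per group = 1 + (1.96 + 0.84)² × 2 × (30/25)² / (4/12)² = 204.2, against 200 stated.

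The stated power above 99% for the primary question (200 per group, difference 15, SD 30) also reproduces, at 99.9%. Neither calculation involves approach.

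**Identification.** At a given visit, the relevant columns are: intercept, arm (1 = group A), approach (1 = posterior) and arm × approach. Four coefficients need four independent columns. Suppose first that nobody in group B is operated.

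- *Unoperated patients set to missing.* Only operated group A patients remain. Arm equals 1 throughout and duplicates the intercept, and arm × approach duplicates approach. Rank 2 of 4.
- *Unoperated patients coded 0.* Approach equals 1 only in group A, so arm × approach is the same column as approach. Rank 3 of 4.

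In both cases the interaction is not identified. Rank 4 is reached only when group B contains late operations by both approaches.

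**What is estimated once group B has late operations.** With unoperated patients missing, the coefficient is

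(posterior − anterior among operated A) − (posterior − anterior among operated B).

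Operated A leaves out those who recovered before surgery. Operated B consists mainly of those who worsened or had not improved at six months. Both sets are defined by events after randomisation. Time since surgery also differs: at the 12-month visit a group A patient operated at 2–4 weeks is about 11 months past surgery, whereas a group B patient operated after the six-month offer is at most about 6 months past it. Coding unoperated patients 0 does not help, because the reference level in group B then mixes late anterior operations with patients never operated.

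**Precision.** The protocol gives no rate of late surgery and no share of posterior operations, so both are assumed and varied. Also assumed: 95% of group A operated (190 of 200), and SD 30 mm as in Sample size. For the operated-only fit at 12 months,

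SE = 30 × √(1/A_ant + 1/A_post + 1/B_ant + 1/B_post), using expected counts.

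| Group B operated | Posterior share | A ant / post | B ant / post | Sum of reciprocals | SE (mm) |
|---|---|---|---|---|---|
| 10% (20) | 10% | 171 / 19 | 18 / 2 | 0.614 | 23.5 |
| 10% (20) | 30% | 133 / 57 | 14 / 6 | 0.263 | 15.4 |
| 25% (50) | 10% | 171 / 19 | 45 / 5 | 0.281 | 15.9 |
| 25% (50) | 30% | 133 / 57 | 35 / 15 | 0.120 | 10.4 |
| 40% (80) | 10% | 171 / 19 | 72 / 8 | 0.197 | 13.3 |
| 40% (80) | 30% | 133 / 57 | 56 / 24 | 0.085 | 8.7 |

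For comparison, a binary baseline modifier with prevalence p, known in all 400 patients, has SE = 30 × √(2/(200p) + 2/(200(1 − p))): 10.0 mm at p = 0.1, 6.5 mm at p = 0.3 and 6.0 mm at p = 0.5.

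**The case against.** The strongest reply is that the protocol plans for surgery in group B, so the model will probably run. That is correct. A reader might infer from the mismatch that the interaction can never be estimated. The documents do not support that, because surgery if needed is part of the conservative strategy and some group B patients will have a recorded approach. What remains is that the coefficient answers a different question from the one stated.

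A second reply is that the as-treated analysis covers approach. It does not. If the groups are redefined by treatment received, no conservatively treated patient has an approach, and the interaction is again not identified.

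A third reply is that a journal article condenses the full protocol. That would excuse an omission, but here the article names both the variable and the model.

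A fourth reply concerns weight, and it stands. Approach is one item in an exploratory secondary analysis. Variables are added singly, so the problem does not spread to the other modifiers. The subgroup hypotheses in Conclusion and Discussion name more neck pain than arm pain and type D personality, not approach.

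A reader might also picture the whole of group A set against late-operated group B patients. That goes too far: group A patients who recover before surgery have no approach either, so the selection occurs in both groups.

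**Conclusion.** The concern holds in this form: as specified, the approach-by-arm term is either not identified (no surgery in group B) or computable only as a contrast between groups selected after randomisation, which is not modification of the intention-to-treat difference. This follows from the text and does not depend on any assumed rate. Only the standard errors of about 9 to 24 mm rest on assumptions: 10–40% late surgery in group B, 10–30% posterior operations, 95% of group A operated, SD 30 mm.

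A reader might infer that the trial's main results are compromised. They are not: the 1-year difference between arms, the duration interaction, the total of 400 and the cost-utility analysis do not use approach. Severity is minor to moderate.

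**What to change.** In Statistical analysis, Secondary outcome, delete surgical approach from the variables tested by interaction with arm. Add a sentence saying that anterior and posterior operations will be compared descriptively among operated group A patients, and that the comparison is not randomised because the surgeon chose the approach. The cost is wording only; the standardised procedure form should already supply the data.

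Recording an intended approach for every patient before allocation would give a valid modifier in principle, but it is not a simple substitute here. Recruitment began in August 2012, so patients already randomised could not be covered. The visit before randomisation may also be to a neurologist, in which case no operating surgeon's intention may be available.
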